### **6.2.4.2 Analysis unit**

The statistical unit for this analysis will be the 6-month persistent cervical HPV infection for which it is assessed that a following histopathologically-confirmed CIN2+ (or CIN1+, or CIN3+) associated with the same HPV type is detected.

### 6.2.4.3 Event variable

The analyzed event - histopathologically-confirmed CIN2+ (or CIN1+, or CIN3+) associated with the same HPV type as the 6-month persistent cervical HPV infection - will be analyzed by means of a binary variable with the following categories:

- 1 = Detection of a histopathologically-confirmed CIN2+ (or CIN1+, or CIN3+) associated with the same HPV type as the 6-month persistent cervical HPV infection
- 0 = No detection of a histopathologically-confirmed CIN2+ (or CIN1+, or CIN3+) associated with the same HPV type as the 6-month persistent cervical HPV infection or no detection of a histopathologically-confirmed CIN2+ (or CIN1+, or CIN3+)

In case more than one histopathologically-confirmed CIN2+ (or CIN1+, or CIN3+) associated with a confirmed 6-month persistent cervical HPV infection are detected, only the first CIN2+ (or CIN1+, or CIN3+) in chronological order will be taken into account, whether the histopathologically-confirmed CIN2+ (or CIN1+, or CIN3+) is detected prior, i.e. within the 12 months preceding the confirmed 6-month persistent cervical HPV infection or after this infection.

The event will be determined as showed with the following examples (See section 8.4.1 for more details):

| Sub-
ject | Detected cervical HPV infections* and/or lesions
over the follow-up period                                                                                                                                                   | Subject
included in
analysis
population | Event
(0 = No /
1 = Yes) |
|--------------|---------------------------------------------------------------------------------------------------------------------------------------------------------------------------------------------------------------------------------|--------------------------------------------------|--------------------------------|
| A            | -                                                                                                                                                                                                                               | No                                               |                                |
| B            | Transient infection associated with HPV type X
CIN associated with HPV type X                                                                                                                                                | No                                               |                                |
| C            | 12-month persistent infection associated with HPV type X
CIN associated with HPV type X                                                                                                                                      | Yes                                              | 1                              |
| D            | Transient infection associated with HPV type X
Transient infection associated with HPV type Y
6-month persistent infection associated with HPV type Z
CIN associated with HPV type X
CIN associated with HPV type Z | Yes                                              | 1                              |
| E            | 6-month persistent infection associated with HPV type X                                                                                                                                                                         | Yes                                              | 0                              |
| F            | 6-month persistent infection associated with HPV type X
6-month persistent infection associated with HPV type Y
CIN associated with HPV type X                                                                            | Yes                                              | 1
0                         |
| G            | 6-month persistent infection associated with HPV type X**
6-month persistent infection associated with HPV type X
CIN associated with HPV type X                                                                          | Yes                                              | 0
1                         |

\* Cervical HPV infections of same HPV type are separated by a clearance.

**\*\*** In case two distinct 6-month persistent infections (i.e. separated by a clearance), associated with the same HPV type, are detected for a same subject, the following rules will apply:

- the event will be associated with the first detected infection (in chronological order) if a CIN2+ (or CIN1+, or CIN3+) associated with this HPV type is detected after the first detected infection but before the second detected infection of same type,
- the event will be associated with the second detected infection (in chronological order) if a CIN2+ (or CIN1+, or CIN3+) associated with this HPV type is detected after the second detected infection.

(See Section 4.3.1 and flowchart in Section 8.2 for the definition and determination of incident, transient, persistent and other cervical HPV infections ; See Sections 4.3.2 to 4.3.4 for the definition of histopathologically-confirmed CIN2+ (or CIN1+, or CIN3+) associated with a given HPV type ; See Section 8.3.1 for the flowchart of data associated with this objective).

#### **6.2.4.4 Time computation**

The time between the onset of a confirmed persistent cervical HPV infection (6-month definition) and a histopathologically-confirmed CIN2+ (or CIN1+, or CIN3+) associated with the same HPV type will be calculated in days as: Date of event or Date of censoring - Date of detection of the 6-month HPV persistent infection.

The date of event will be:

- the date of the detection of the histopathologically-confirmed CIN2+ (or CIN1+, or CIN3+) associated with the same HPV type as the HPV type of the 6-month persistent cervical HPV infection,

The date of censoring will be:

- the date of Month 48 visit for subjects who attended all visits during the 48-month follow-up period and who had a histopathologically-confirmed CIN2+ (or CIN1+, or CIN3+) not associated with the same HPV type as the 6-month persistent cervical HPV infection or who did not have a histopathologically-confirmed CIN2+ (or CIN1+, or CIN3+) or during this period,
- the date of the last PCR reported at the latest visit for which data are available or the date of the last cytology or the date of the last biopsy (if the date is after the date of the last PCR) for subjects who did not attend all visits during the 48-month follow-up period and who had a histopathologically-confirmed CIN2+ (or CIN1+, or CIN3+) not associated with the same HPV type as the 6-month persistent cervical HPV infection or who did not have a histopathologically-confirmed CIN2+ (or CIN1+, or CIN3+) throughout their follow-up period (from first to last visit).
- Special cases:
  - In case two distinct 6-month persistent cervical HPV infections (i.e. separated by a clearance) associated with the same HPV type are detected for a same subject and a histopathologically-confirmed CIN2+ (or CIN1+, or CIN3+) associated with this HPV type is detected after the second infection, the date of censoring of the first infection will be the date of onset of the second infection since the event (i.e. detection of a histopathologically-confirmed CIN2+ (or CIN1+, or CIN3+)) is associated with the second detected infection (in chronological order).

- In case a histopathologically-confirmed CIN2+ (or CIN1+, or CIN3+) associated with a given HPV type is detected before the detection of the first 6-month persistent cervical infection of that HPV type, the time between the 6-month persistent cervical infection and the histopathologically-confirmed CIN2+ (or CIN1+, or CIN3+) will be set to 0 (i.e. the date of the 6-month persistent infection will be that of the histopathologically-confirmed CIN2+ (or CIN1+, or CIN3+)) if the delay between the histopathologically-confirmed CIN2+ (or CIN1+, or CIN3+) and the 6-month persistent cervical infection is less than 12 months (if the delay is more than 12 months, the event is censored).

These cases are illustrated in the following table. The associations between the histopathologically-confirmed CIN2+ (or CIN1+, or CIN3+) and confirmed 6-month persistent cervical infections are showed in bold.

| Visit                                                                | Visit                                     | Visit                                     | Visit                               |
|----------------------------------------------------------------------|-------------------------------------------|-------------------------------------------|-------------------------------------|
| No CIN x                                                  | HPV x persistent 6 month       | No CIN x                       | No CIN x                 |
| No CIN x                                                  | HPVx persistent 6 month | CINx                    | /                                   |
| No CIN x                                                  | HPVx persistent 6 month | CINx                    | HPV x persistent 6 month |
| No CIN x                                                  | HPV x persistent 6 month       | HPVx persistent 6 month | CINx              |
| CIN x > 12 months before persistent HPV x      | HPV x persistent 6 month       | /                                         | /                                   |
| CINx ≤ 12 months before persistent HPVx | HPVx persistent 6 month | /                                         | /                                   |

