### 3.2 Study procedures resulting in data to be used for analyses

- Blood samples for all subjects were drawn at Months 0, 7 and 24 and in a subset of subjects from selected study sites.
- Gynecological examinations were performed at Months 0, 12, 24, 36 and 48.
- Cervical liquid-based cytology samples were collected at Months 0, 6, 12, 18, 24, 30, 36 and 48:
  - HPV DNA typing by PCR was performed on cervical liquid-based cytology samples at Months 0, 6, 12, 18, 24, 30, 36 and 48,
  - Cytopathological examinations were performed on liquid-based cytology samples to detect abnormal cells at Months 0, 12, 24, 36 and 48 in all subjects,
  - Screening for *Chlamydia trachomatis* and *Neisseria gonorrhoeae* on liquid-based cytology samples at Months 0, 12, 24, 36 and 48.

Note: As of Protocol Amendment 2, screening for *Neisseria gonorrhoeae* was done only if considered appropriate by the investigator.

- Colposcopic referral according to appropriate clinical management algorithms. A central laboratory processed and interpreted results from liquid-based cytology and histology samples. All CIN endpoints were confirmed by an expert histopathology review panel that was blinded to vaccine status, HPV DNA status before biopsy and cytology reports. An Endpoint Committee was responsible for reviewing all available clinical and laboratory data prior to study unblinding by the external statistician to make final case assignments for all subjects assumed to meet criteria for primary and secondary efficacy endpoints.

- Behavioral questionnaire completed by interview for all subjects at Months 1, 12, 24, 36 and 48. The behavioral questionnaire (self-administered) collected specific socio-demographic and behavioral data concerning determinants that are recognized to predispose subjects to cervical HPV infection or are recognized co-factors for cervical carcinogenesis. The baseline questionnaire assessed at Month 1 collected data which occurred during past history and during the previous year. Questionnaires assessed at Month 12, 24, 36 and 48 collected data assessed during the previous year.

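### Section 6.2.4.4 ends a first persistent infection at the onset of a same-type repeat only if a CIN follows, so censoring depends on the later outcome

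*SAP*

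**What the plan says.** **Unit and clock.** Section 6.2.4.2: "The statistical unit for this analysis will be the 6-month persistent cervical HPV infection". Two same-type infections in one woman are therefore two records. Section 6.2.4.4 gives each its own clock: "Date of event or Date of censoring - Date of detection of the 6-month HPV persistent infection".

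**Attribution.** When a CIN is found after the second of two same-type persistent infections, section 6.2.4.3 states that "the event will be associated with the second detected infection (in chronological order"). Example G in that section codes the first infection 0 and the second 1.

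**General censoring.** Section 6.2.4.4 censors records without a same-type CIN at "the date of Month 48 visit for subjects who attended all visits during the 48-month follow-up period". For the other women it uses "the date of the last PCR reported at the latest visit for which data are available", or a later cytology or biopsy.

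**Special case.** The same section shortens the first record only where a same-type CIN is found after the second infection; in that case "the date of censoring of the first infection will be the date of onset of the second infection since the event" is assigned to the second. The table that follows shows two same-type infections without an intervening CIN only in a row that ends in CIN. Neither that table nor Annex 9.4.1 covers two same-type infections with no CIN, so the general rule governs them.

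Section 6.2.5.4 repeats the special case for any cervical HPV infection.

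**The concern.** Take two women with identical histories up to the onset of a second same-type persistent infection. If one later develops CIN, her first record stops at that onset. If the other does not, her first record continues to Month 48. Only a future event separates them, so censoring of the first record is not independent of outcome.

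The plan's reason for shortening the record is that a later CIN belongs to the second infection. That applies equally to the woman without CIN: her first record cannot have an event after the second onset either, yet it stays in the risk set while her second record covers the same calendar months.

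The extra time is event-free and comes only from non-cases, so it enlarges denominators without adding events. At stake are the Kaplan-Meier curves, log-rank tests and Cox models for the primary CIN2+ endpoint, and for CIN1+ and CIN3+ after persistent infection. HPV type is the main variable of interest in Annex 9.5.1. If types differ in how often they are re-detected after clearance, the padding differs by type.

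**Working it through.** **1. Reproduce the plan's own figures (Annex 9.4.1).** Time = event or censoring month minus onset month.
- Example #3: 48 − 12 = 36, censored, as printed.
- Example #4: 48 − 24 = 24, censored, as printed.
- Example #1: 30 − 6 = 24, event, as printed.

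**2. One woman, onsets at Months 6 and 24, followed to Month 48.**
- No CIN, as written: (48 − 6) + (48 − 24) = 42 + 24 = 66 infection-months.
- CIN at Month 48, as written: (24 − 6) + (48 − 24) = 18 + 24 = 42.
- First record always stopped at the second onset: 42 in both cases.

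The 24 months after the second onset count twice for the non-case only.

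**3. All possible pairs.** Section 3.2: "HPV DNA typing by PCR was performed on cervical liquid-based cytology samples at Months 0, 6, 12, 18, 24, 30, 36 and 48". A 6-month persistent infection needs positives spanning more than 150 days (section 4.3.1). I took two positives, at least one negative, then two positives, with no missed visits. With onsets a and b, a non-case has (48 − a) + (48 − b) months as written and 48 − a without duplication. Her first record is (48 − a)/(b − a) times as long as that of a woman with the same onsets and a CIN after the second.

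| Onsets a/b | As written, no CIN | Unduplicated | Ratio | First record, non-case vs case |
|---|---|---|---|---|
| 0/18 | 78 | 48 | 1.63 | 2.67 |
| 0/24 | 72 | 48 | 1.50 | 2.00 |
| 0/30 | 66 | 48 | 1.38 | 1.60 |
| 0/36 | 60 | 48 | 1.25 | 1.33 |
| 6/24 | 66 | 42 | 1.57 | 2.33 |
| 6/30 | 60 | 42 | 1.43 | 1.75 |
| 6/36 | 54 | 42 | 1.29 | 1.40 |
| 12/30 | 54 | 36 | 1.50 | 2.00 |
| 12/36 | 48 | 36 | 1.33 | 1.50 |
| 18/36 | 42 | 30 | 1.40 | 1.67 |

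**4. Event rate in women with onsets at Months 6 and 24.** Assume a constant CIN hazard λ per month (the SAP gives none). Expected first-record time is (1 − e^(−18λ))/λ if it always stops at Month 24. As written, 24·e^(−42λ) is added for women still without CIN at Month 48. The first record's events are the same either way, so the rate changes by the ratio of the times.
- λ = 0.002: 17.68 / (17.68 + 22.07) = 17.68/39.75 = 0.44
- λ = 0.005: 17.21/36.67 = 0.47
- λ = 0.01: 16.47/32.24 = 0.51

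Over both records, with unduplicated time (1 − e^(−42λ))/λ, the ratios are 40.28/62.35 = 0.65, 37.88/57.34 = 0.66 and 34.30/50.06 = 0.69.

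**5. Effect on the whole analysis.** The SAP does not state what share of infections is followed by a same-type repeat. A simulation assumed shares of 2% to 20%, constant CIN rates of 2, 5 and 10 per 100 infection-years, onset pairs drawn evenly from the ten above, and full follow-up. Total infection-time as written, divided by unduplicated time:

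| Repeat share | Rate 2 | Rate 5 | Rate 10 |
|---|---|---|---|
| 2% | 1.0114 | 1.0107 | 1.0094 |
| 5% | 1.0280 | 1.0266 | 1.0234 |
| 10% | 1.0555 | 1.0520 | 1.0472 |
| 20% | 1.1065 | 1.1007 | 1.0904 |

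At a 10% share and a rate of 5, the observed rate falls from 4.99 to 4.74 per 100 infection-years. If two determinant groups had shares of 5% and 10%, their crude rate ratio would shift by 1.0520/1.0266 = 1.025, about 2.5%.

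**The case against.** **The effect may be small.** A persistent repeat needs two positives, a negative and two more positives of one type within eight PCR visits. This stands: the overall effect may be only about 1%.

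**The model may absorb it.** Section 6.2.4.5 provides robust variances and leaves open a counting-process layout. Robust variances correct standard errors, not risk sets or person-time. A counting-process layout could avoid the overlap in the Cox model, but it is not fixed, and section 6.2.4.4 sets the dates that the Kaplan-Meier curves and log-rank tests use.

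**Stronger readings that the documents do not support:**
- A reader might infer that non-cases contribute double person-time. Only women with a same-type repeat are affected, and only their time after the second onset counts twice.
- A reader might take the ratios of 0.44 to 0.51 as the bias in the trial's results. They describe the first record alone, if every woman had onsets at Months 6 and 24.
- A reader might carry the argument unchanged to any infection. Under section 6.2.5.3 and the tables in 6.2.5.4, a later CIN goes first to a 6-month persistent infection, whatever the order of the infections. A persistent infection followed by a transient one can then still receive the event, so its time after the second onset is legitimately at risk. The special case in 6.2.5.4, which gives the CIN to the second infection, conflicts with that hierarchy.
- A reader might add the endpoint density to the list. Section 6.2.3.1 divides by person-months of subjects at risk, which need not be summed over infection records.

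**Conclusion.** The defect stands for section 6.2.4.4, and so for the primary CIN2+ analysis and the CIN1+ and CIN3+ analyses after persistent infection. Censoring of the first record is conditioned on a later event, and nothing else in the SAP repairs it.

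The direction for Kaplan-Meier risk and infection-based rates is downward. For hazard ratios, bias is possible where a determinant is linked to same-type re-detection; its size was not computed beyond the crude rate-ratio illustration.

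The 1.25 to 1.63 range follows from the visit schedule for two infections and complete follow-up, taking one negative sample as enough to separate them. The overall 1% to 11% rests on assumed repeat shares and constant rates. For the any-infection analysis, what can be said is that the attribution rules conflict and that the special case there also depends on a later CIN.

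**What to change.** **Section 6.2.4.4.** Remove the condition that a CIN is detected after the second infection. End the first record at the onset of the next same-type 6-month persistent infection for every woman, whether or not a CIN follows. Add a table row for two same-type infections without CIN.

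This loses no event, because section 6.2.4.3 already gives later CINs to the second infection. The cost is one sentence, slightly less event-free person-time, and a rerun. Section 7 records that the primary analysis was delivered in August 2011, so that result is included in the rerun. Reporting the number of same-type repeats by HPV type would show how much the change matters.

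**Section 6.2.5.4.** First reconcile the special case with the hierarchy in 6.2.5.3 and the tables. Then end each record, regardless of later CIN, at the point after which a new CIN could no longer be assigned to it. This takes more than one sentence: copying the 6.2.4.4 wording would cut records off before events that the hierarchy assigns to them.

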## 4 DATA EVALUATION

### 4.1 Endpoints

#### 4.1.1 Primary endpoint

- Histopathologically-confirmed **CIN2+** associated with the same HPV type as a previous confirmed **persistent cervical HPV infection (6-month definition)**.

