#### 4.3.1 Cervical HPV infections

- **Incident cervical HPV infection:** an incident cervical infection with a given HPV type is defined as the new detection of this HPV type (by PCR) at any time point during the follow-up period (i.e. after enrolment in the control arm of study HPV-008).
- **Transient cervical HPV infection:** a transient cervical infection with a given HPV type is defined as the detection of this HPV type (by PCR) at any single time point during the follow-up period followed by a negative sample for that HPV type at the evaluation performed 6 months after the evaluation when the cervical HPV infection was first detected.
- **6-month persistent cervical HPV infection:** a persistent cervical HPV infection (6-month definition) is defined as the detection of the same HPV type (by PCR) in cervical samples at two consecutive evaluations over approximately a 6-month interval. Thus, the algorithmic definition of a 6-month persistent infection is that there exists a sequence of positive samples with the same HPV type, not interrupted by negative samples, such that the total range is more than 5 months ( $> 150$  days). The start of the persistent cervical HPV infection is defined as the date of the first positive sample in the sequence.
- **12-month persistent cervical HPV infection:** a persistent cervical HPV infection (12-month definition) is defined as the detection of the same HPV type (by PCR) at all available time points over approximately a 12-month interval. Thus, the algorithmic definition of a 12-month persistent cervical infection is that there exists a sequence of positive samples with the same HPV type, not interrupted by negative samples, such that the total range is more than 10 months ( $> 300$  days). The start of the persistent cervical HPV infection is defined as the date of the first positive sample in the sequence.
- **Other cervical HPV infection:** other cervical HPV infections than those described above will be considered in the analysis. These infections are cervical HPV infections with duration less than 150 days and cervical HPV infections detected at the last visit and for which it is not possible to determine if they are transient or persistent.

- **Clearance of cervical HPV infection:** two definitions will be used:

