## **6.2.4 Analysis of time between persistent cervical HPV infections and lesions**

### **6.2.4.1 Population**

The population for the analysis of time between confirmed persistent cervical HPV infections (6-month definition) and histopathologically-confirmed CIN2+ (or CIN1+, or CIN3+) associated with the same HPV type will be restricted to subjects from the TVC-1-Control arm cohort for whom at least one 6-month persistent cervical HPV infection was detected so that a starting date is available for the computation of the time between persistent infections and lesions.

Subjects with positive or missing HPV DNA at Month 0 for the HPV type associated with the endpoint will be taken into account in the analysis as well as subjects for whom a histopathologically-confirmed CIN2+ (or CIN1+, or CIN3+) associated with a given HPV type is detected prior to the detection of the first 6-month persistent cervical infection of that HPV type (see Sections 6.2.4.3 and 6.2.4.4 for handling this particular case).

The cervical HPV infections of subjects positive for HPV DNA at Month 0 and negative for HPV DNA at Month 6 (for the HPV type associated with the endpoint) will be considered as transient cervical HPV infections. As a matter of fact, such cervical HPV infections may be either transient or persistent but the start date of infections which started before study entry is unknown. Consequently, these infections will not be taken into account in the analyses.

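### The primary onset-to-CIN2+ times include zeros assigned to lesions found before the infection, and time since enrolment for infections already present at Month 0

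*SAP*

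**What the plan says.** **What is to be estimated.** Section 6.2.4.4 defines it as "The time between the onset of a confirmed persistent cervical HPV infection (6-month definition) and a histopathologically-confirmed CIN2"+ of the same type. The primary endpoint (4.1.1) is a lesion "associated with the same HPV type as a previous confirmed" persistent infection. The analysis unit (6.2.4.2) is an infection "for which it is assessed that a following histopathologically-confirmed CIN2"+ is detected. In all three places the infection comes first.

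**Lesions found before the infection.** Section 6.2.4.3 counts the first lesion even when it "is detected prior, i.e. within the 12 months preceding the confirmed 6-month persistent cervical HPV infection or after this infection". Section 6.2.4.4 says that the time for such a lesion "will be set to 0 (i.e. the date of the 6-month persistent infection will be that of the histopathologically-confirmed CIN2"+, provided that the delay "is less than 12 months (if the delay is more than 12 months, the event is censored").

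**Infections present at entry.** Section 4.3.1: "The start of the persistent cervical HPV infection is defined as the date of the first positive sample in the sequence". Section 6.2.4.1 keeps subjects whose Month 0 DNA result for the type is positive or missing. It leaves out only infections positive at Month 0 and negative at Month 6, and in doing so notes that "the start date of infections which started before study entry is unknown".

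**What uses these times.** Section 6.2.4.5 feeds them to Kaplan-Meier curves, log-rank tests and Cox models, and reports mean and median times and hazard ratios. The covariate list in 9.5.1 names HPV type as the main variable of interest and has no term for infections present at entry versus acquired later. The only sensitivity analyses named (4.5.2) concern imputed data.

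**The concern.** Two kinds of record enter the primary analysis with a time that is not the time from onset to lesion.

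- For a lesion found before the infection, the observed order contradicts the endpoint. The plan resolves this by overwriting the infection date. If the type found in the lesion shows that infection was already there, the true time is some unknown positive value. If it does not, the lesion did not follow the infection. Zero is a convention in both cases.
- For an infection already present at Month 0, the clock measures time since enrolment. The recorded time is only a lower bound on the time from onset.

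Both feed the curves and the mean and median times directly. If their shares differ between HPV types, they also distort the hazard ratios for the plan's main covariate.

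**Working it through.** **1. The plan's own examples (9.4.1).** Time is the date of lesion or censoring minus the first positive sample.
- Subject 1: 30 − 6 = 24 months
- Subject 3: 48 − 12 = 36 months
- Subject 4: 48 − 24 = 24 months

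All three agree with the SAP and confirm that the clock starts at the first positive sample. No example shows a Month 0 positive infection or a prior lesion.

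**2. The Month 0 start.** No single sentence states it. It follows from 4.3.1 (onset is the first positive sample) and 6.2.4.1 (Month 0 positives are kept). If the Month 0 result is missing, the start is the first later positive sample and onset is equally uncertain. By contrast, HPV typing was done every 6 months up to Month 36 (section 3.2). A persistent infection that was negative at Month 0 therefore has its onset bracketed to about 6 months when visits are attended. An infection present at entry has no such bound.

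**3. Time-0 events and Kaplan-Meier.** If a share f of infections has an assigned time-0 event and the others have cumulative risk F(t), the curve shows F*(t) = f + (1 − f)F(t). F and f are assumed here; the SAP gives neither.

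| f | 12 months (F = 3%) | 24 months (F = 6%) | 36 months (F = 9%) |
|---|---|---|---|
| 0.5% | 3.5% | 6.5% | 9.5% |
| 1% | 4.0% | 6.9% | 9.9% |
| 2% | 4.9% | 7.9% | 10.8% |
| 5% | 7.9% | 10.7% | 13.6% |

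For example, at 12 months with f = 1%: 0.01 + 0.99 × 0.03 = 0.0397.

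**4. Time-0 events and the HPV-16 hazard ratio.** This is a simulation of a standard Cox model with assumed inputs: 4,000 infections, 15% HPV-16, other-type hazard 0.002 per month, true hazard ratio 2.5, censoring uniform over 6 to 48 months, 40 runs per row.

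| f, HPV-16 | f, other | Hazard ratio, time-0 events kept | Dropped |
|---|---|---|---|
| 1% | 1% | 2.30 | 2.52 |
| 2% | 1% | 2.37 | 2.45 |
| 2% | 0.5% | 2.64 | 2.49 |
| 5% | 1% | 3.00 | 2.55 |
| 5% | 0.5% | 3.17 | 2.44 |

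**5. Month 0 start.** Recorded time = true time − u, where u is the months infected before Month 0. A true 30 months is recorded as 24, 18 or 6 months for u = 6, 12 or 24.

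For risk, assume a Weibull time from onset with 15% risk at 48 months: H(t) = −ln(0.85) × (t/48)^k = 0.1625 × (t/48)^k, and u = 12. The 12-month risk from true onset is 1 − exp(−H(12)). The risk recorded from Month 0 is 1 − exp(−[H(24) − H(12)]).

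| Shape k | H(12) | H(24) − H(12) | From onset | From Month 0 | Ratio |
|---|---|---|---|---|---|
| 0.7 | 0.0616 | 0.0385 | 6.0% | 3.8% | 0.63 |
| 1.5 | 0.0203 | 0.0371 | 2.0% | 3.6% | 1.81 |
| 2.0 | 0.0102 | 0.0305 | 1.0% | 3.0% | 2.97 |

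The ratio is 1 only at constant hazard (k = 1). Each row contrasts a wholly prevalent with a wholly incident group. The plan's pooled cohort falls between the two, according to its unreported mix.

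**The case against.** The plan is open about what it does. Section 2.2 explains why it speaks of detected infections, 6.2.4.4 measures from detection, and 4.2 and 6.2.4.1 say that Month 0 positives are included. Infections positive at Months 0 and 6 meet the persistence definition, whereas for those negative at Month 6 persistence cannot be established, so treating the two groups differently is not arbitrary. That stands as a reason for keeping them in a study of progression. It does not supply an onset date, and the objective is time from onset.

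A reader might infer more than the SAP supports:

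- *That covariates for time-0 events postdate the lesion.* Section 4.4.3 takes behavioural data from before the reference infection, and the rule moves that infection to the lesion date. The plan does not say which date anchors the covariates, so this is not established.
- *That Kaplan-Meier and Cox would use different events because a zero-length interval drops out.* A counting process is only one of the approaches listed in 6.2.4.5. In a standard Cox model time-0 events do contribute, as step 4 shows.
- *That starting the clock at the first positive, while requiring positives more than 150 days apart, wipes out early events.* This would need every early lesion to be treated and every treatment to end positivity before the next sample. Section 4.3.2 allows confirmation on biopsy alone, and a lesion between two positive samples still counts. Entering infections only at the confirming sample would also conflict with counting lesions from onset.

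**Conclusion.** The point holds for the two rules described. As written, the primary analysis counts lesions found before the infection at an assigned time of 0, against its own endpoint and analysis unit. It also gives infections present at entry a start date that the SAP admits is not their onset. The curves, the mean and median times and, where the shares differ by type, the hazard ratios are affected.

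A reader might infer a bias of known direction. The documents do not support that: they give no number of time-0 events or of Month 0 positive persistent infections. The illustrated 12-month risk ratio runs from 0.63 to about 3.0, and a true hazard ratio of 2.5 moves to between about 2.3 and 3.2. All of these rest on the assumed inputs shown. The plan should be changed before the manuscript; the point does not show that the results are wrong.

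**What to change.** - Take the onset-to-CIN2+ times (Kaplan-Meier, mean, median) from infections whose type was DNA-negative at Month 0, counting only CIN2+ on or after the first positive sample. Section 4.2 says that earlier analyses of this cohort already required type-specific negativity at Month 0, so the subset can be defined from existing data.
- Stratify the Cox baseline hazard by positive or missing versus negative at Month 0, and show Kaplan-Meier curves separately for the two strata.
- Keep the time-0 rule as a sensitivity analysis. State how infections with a prior same-type CIN2+ are handled in the main analysis.
- Report the numbers of time-0 events and of Month 0 positive infections.
- Reconcile the window in 6.2.4.4: the text requires a delay under 12 months and the table allows exactly 12.
- Do the same for the any-infection analysis (6.2.5), which has the same time-0 rule and also keeps infections positive at Month 0 and negative at Month 6.
- Section 7 says that the primary analysis was delivered in August 2011, so label the revision post hoc and show it beside the delivered result.

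The cost is SAP wording and a rerun, with no new data. Some events leave the main time estimates and intervals widen.
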